#### Descriptive statistics

Patient characteristics will be described by treatment group and for the entire sample of patients. Quantitative variables will be presented as means with standard deviations or in cases of skewed distribution as medians and interquartile ranges. Qualitative data will be presented as absolute and relative frequencies.

#### Inferential statistics

Differences in the main variable (change in Hb levels from POD 1 to POD 30) between the treatment groups will be tested by means of an analysis of covariance (ANCOVA) using Hb at POD 1 as covariable. Chi-square test will be used for the key secondary variable, percentage of patients with Hb levels at POD 30 ≥ 13 g/dL, as well as for other categorical variables. For categorical ordinal variables the ANOVA or Kruskall–Wallis test will be used. Continuous variables will be analysed by means of T-test or the corresponding non-parametric tests. A subgroup analysis for the stratification variable (Hb < 10 g/dL and Hb ≥ 10 g/dL) is planned.

An exploratory multivariate analysis will be performed to identify characteristics of patients associated to larger changes in Hb levels and to identify subgroups of patients that may benefit most of the single IVI dose.

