### Randomisation

A computer-generated block randomisation (block size 8) has been created with WinPepi etcetera module version 3.26. Randomisation has been stratified by Hb level on day 1 (Hb < 10 g/dL or Hb ≥ 10 g/dL). Sealed envelopes have been created for each individual patient. Pre-screened patients are randomly assigned to one of the two study treatments on POD 1 and after knowing the results of the blood tests for Hb levels.

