### Study procedures

During the preoperative anaesthesiology visit, patients meeting eligibility criteria will be informed and those willing to participate in the study will sign the ICF. During this visit, and after signing the ICF, patients will complete a quality-of-life questionnaire (QL-C30). On POD 1, and after checking eligibility (Hb levels < 11 g/dL), treatment will be randomly assigned to one of the two treatment arms. After hospital discharge, patients will come for a visit on POD 30 when blood tests assessing iron metabolism and Hb will be performed and patients will be asked to complete the QL-C30 questionnaire. Any additional blood tests assessing Hb levels and iron metabolism performed from patient diagnosis to end of trial (i.e. at diagnosis, immediately before surgery and on POD 4 or hospital discharge) will be recorded. When patients are hospitalised, regular checks for adverse events or any complication are performed. Iron treatment will be discontinued in patients admitted in the intensive care unit on POD 1 due to organic fail or presenting Claviens grade 4 complications. Whenever possible, these patients will be followed up to POD 30 (Fig. 2).

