### Study endpoints

The main study endpoint will be the change in Hb levels from POD 1 to POD 30. The percentage of patients with Hb levels ≥ 13 g/dL at POD 30 will be considered as a key secondary endpoint. Other secondary endpoints include: changes in iron metabolism parameters (Fe, ferritin, transferrin, % saturated trasferrin) at POD 30; total doses of iron received up to POD 30; number of postoperative transfusions; percentage of patients not compliant with oral iron treatment; number of medical and surgical complications; adverse reactions reported by the patient; and use of health resources after surgery: number of admissions, length of hospital stay; changes in quality of life (QoL). Potential adverse reactions of IVI are headache, dizziness, nausea, abdominal pain, constipation, diarrhoea, exanthema, hypophosphatemia and increases in alanine-aminotransferase. Hypersensitivity and injection site reactions are rare. Oral iron treatment is associated with gastric intolerance and constipation.

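### The tests fixed for the key secondary endpoint (Hb ≥ 13 g/dL at POD 30) and for change in quality of life are valid but leave out available baseline covariates, at a small cost in precision

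*Protocol article*

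**What the plan says.** Under Study endpoints, the article singles out one secondary endpoint: "The percentage of patients with Hb levels ≥ 13 g/dL at POD 30 will be considered as a key secondary endpoint". Changes in iron parameters and changes in quality of life are among the other secondary endpoints.

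Inferential statistics then names the tests:

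- Primary endpoint, change in Hb from POD 1 to POD 30: "analysis of covariance (ANCOVA) using Hb at POD 1 as covariable".
- Key secondary endpoint: "Chi-square test will be used for the key secondary variable".
- Other continuous endpoints: "Continuous variables will be analysed by means of T-test or the corresponding non-parametric tests".

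Two baseline variables bear on this. Under Randomisation, "Randomisation has been stratified by Hb level on day 1 (Hb < 10 g/dL or Hb ≥ 10 g/dL"). Under Study procedures, at the preoperative visit "patients will complete a quality-of-life questionnaire (QL-C30"), and they complete it again at POD 30. In the analysis of secondary endpoints the stratification factor has no stated role beyond a planned subgroup analysis. The exploratory multivariate analysis concerns change in Hb, so it does not cover these endpoints.

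**The concern.** The responder endpoint is a fixed threshold, so it depends on where the patient starts. A patient at 8 g/dL on POD 1 needs a rise of 13 − 8 = 5 g/dL, and one at 10.9 g/dL needs 13 − 10.9 = 2.1 g/dL. The Discussion expects an average rise of about 2. The design already treats POD 1 Hb as important by stratifying on it and adjusting the primary analysis for it, but the key secondary test leaves it out. When allocation is balanced on a predictive factor and the test ignores that factor, the standard error is somewhat too large and the test becomes conservative.

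For quality of life, a t-test on the change score subtracts the baseline in full, whatever its correlation with the POD 30 score. ANCOVA estimates the weight to give the baseline, which is more efficient and also corrects chance imbalance.

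At stake is precision on secondary endpoints. The responder endpoint deserves the attention because the hypothesis in the Background is worded as achieving normal Hb at POD 30, which this endpoint measures most directly.

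**Working it through.** **The plan's own figure.** Inputs from Sample size: difference 0.75 g/dL, SD 1.3, two-sided 5%, power 80%.

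n per group = 2 × (1.960 + 0.842)² × 1.3² / 0.75² = 2 × 7.85 × 1.69 / 0.5625 ≈ 47.2, rounded up to 48.

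The stated 48 reproduces (power 80.7% by the normal approximation, 79.9% by the exact t-test). It concerns the primary endpoint and is not in dispute.

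**Responder endpoint, by simulation.** From the article: 48 per group, blocks of 8 within the two Hb strata, mean rise 2.0, SD of change 1.3, difference 0.75. Assumed, because the article gives no figure: POD 1 Hb normal with mean 10 and SD 0.7, cut to 7–11 g/dL, and a slope of POD 30 Hb on POD 1 Hb of 0.3 to 1.4. At slope 1.0 the change in Hb does not depend on POD 1 Hb. A slope above 1 means that patients who start higher also rise more, so 1.4 is an extreme case. Results of 4000 trials per scenario:

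| Slope | Responders, sucrose / carboxymaltose | Chi-square power | Mantel-Haenszel by stratum | Logistic with POD 1 Hb | Chi-square type I error |
|---|---|---|---|---|---|
| 0.3 | 10.2% / 25.3% | 51.5% | 50.5% | 51.6% | 4.9% |
| 0.6 | 12.4% / 27.8% | 48.0% | 48.0% | 49.7% | 4.8% |
| 1.0 | 14.8% / 30.4% | 45.1% | 46.8% | 49.5% | 4.4% |
| 1.4 | 17.6% / 33.4% | 43.7% | 47.4% | 51.2% | 4.0% |

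The logistic column is a likelihood-ratio test of treatment with continuous POD 1 Hb in the model. Its nominal gain over chi-square runs from 51.6 − 51.5 = 0.1 to 51.2 − 43.7 = 7.5 points. Mantel-Haenszel changes power by −1.0 to +3.7 points.

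**Allowing for the size of the adjusted test.** Responders are few: at slope 1.0, 48 × (0.148 + 0.304) ≈ 22 in the whole trial. The likelihood-ratio test then rejects slightly too often under the null, which flatters its power. With 8000 trials per scenario and its critical value reset to a true 5%:

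| Slope | Null rejection, chi-square / likelihood ratio | Chi-square power | Likelihood ratio, nominal | Likelihood ratio, true 5% | Difference from chi-square |
|---|---|---|---|---|---|
| 0.3 | 5.6% / 5.9% | 51.0% | 52.0% | 49.2% | −1.8 |
| 0.6 | 5.3% / 6.1% | 47.9% | 49.7% | 46.5% | −1.4 |
| 1.0 | 4.6% / 5.6% | 44.8% | 49.4% | 47.4% | +2.6 |

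The chi-square column is at its nominal critical value. The Monte Carlo standard error of a power near 50% is √(0.25/8000) ≈ 0.6 points. So there is no gain at the weaker slopes and 2 to 3 points at slope 1.0.

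**Quality of life.** With equal variance s² at both visits and correlation r, the per-patient variances are:

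- change score: 2(1 − r)s²
- ANCOVA: (1 − r²)s²
- ratio: (1 − r²) / [2(1 − r)] = (1 + r)/2, so the reduction is (1 − r)/2.

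The article gives no r, so a range is shown. The last column starts from a change-score t-test with 80% power and uses Φ[(1.960 + 0.842)/√ratio − 1.960].

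| r (assumed) | Variance ratio | Reduction | Power with ANCOVA |
|---|---|---|---|
| 0.3 | 0.65 | 35% | about 94% |
| 0.5 | 0.75 | 25% | about 90% |
| 0.7 | 0.85 | 15% | about 86% |

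The 80% is only a reference point. The trial is not powered for quality of life.

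**The case against.** The strongest reply is that nothing here is wrong. Chi-square and t-tests are valid in a randomised trial, choosing the simpler valid test for a secondary endpoint is defensible, and the responder gain is close to nil unless POD 1 Hb predicts well. Mantel-Haenszel on the two strata does not reliably help. The Discussion already warns that quality-of-life changes will be hard to interpret. All of that stands, and it keeps the point minor. It does not remove it: the tests are fixed in the text rather than left open, the covariates are already collected, and the quality-of-life gain follows from a formula whatever the value of r below 1.

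A reader might go further in four ways that the article does not support:

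- **That the error rate is inflated.** The effect of ignoring the stratification factor goes the other way: chi-square becomes slightly conservative as POD 1 Hb becomes more predictive.
- **That baseline quality of life is ignored.** The endpoint is a change, which uses the baseline by subtraction. What is missing is covariate adjustment.
- **That adjustment would rescue the responder endpoint, or that its result could disagree with the primary only because one is adjusted.** Power stays near 50% either way, because the weakness comes mainly from dichotomising Hb. Chi-square and adjusted logistic regression gave different significance verdicts in only 2–7% of simulated trials.
- **That iron parameters should be adjusted for POD 1 Hb.** No figure in the article links the two, so a benefit is not shown.

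**Conclusion.** The point holds as a modest loss of precision on secondary endpoints. It is neither a bias nor a threat to the primary analysis.

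For Hb ≥ 13 g/dL the realistic gain from adjusting for POD 1 Hb is about 0 to 3 percentage points of power for slopes of 0.3 to 1.0. It would be larger only if patients with higher POD 1 Hb also rose more. Chi-square is slightly conservative when POD 1 Hb is predictive, with type I error about 4.4% at slope 1.0. These figures rest on an assumed POD 1 Hb distribution and slope.

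For quality of life the variance reduction is 15% to 35% for r from 0.7 to 0.3, assuming equal variances at the two visits. Confidence is high on direction and moderate on size. Priority is minor.

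**What to change.** Before outcome comparisons are seen, record the following in the analysis plan:

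- **Hb ≥ 13 g/dL at POD 30:** a POD 1 Hb-adjusted analysis. The preferred form is logistic regression with treatment and continuous POD 1 Hb, reported as a standardised risk difference with a confidence interval. Mantel-Haenszel by the two Hb strata is a simpler alternative that recovers less. Keep chi-square as supportive.
- **Quality of life:** ANCOVA of the POD 30 score with the pre-surgery score as covariate.
- **Iron parameters:** ANCOVA on a pre-randomisation value, only where one exists. Study procedures records earlier iron tests if they were done, and the POD 4 or discharge sample is taken after randomisation, so it cannot serve as baseline. Do not add POD 1 Hb as a covariate for these.

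No extra patients or measurements are needed. The cost is wording plus a dated justification: the trial is open-label, its tests are published and 75 patients had been randomised when the article was written, so a later change of test would be hard to defend.

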### Feasibility

Despite the large number of elective CRC surgeries performed in our hospital (200 CRC surgeries are performed each year on average), recruitment is limited by the fact that only patients with Hb levels < 11 g/dL can be included. Recruitment started in September 2015 and is planned to finish in September 2018.

### Ethics

Written informed consent will be obtained from each participant before any trial-related procedures are carried out. This trial is being conducted in accordance with the Declaration of Helsinki and good clinical practice principles. The study protocol (Version 2, April 2015) was approved by the Research Ethics Committee of *Corporació Parc Taulí* in April 2015 and by the Spanish Medicines Agency (*Agencia Española de Medicamentos y Productos Sanitarios*) in July 2015. The study is registered in the EU Clinical Trials Register (EudraCT: 2015–001005-13). The present study protocol has been written according to the Recommendations for Interventional Trials (SPIRIT) 2013 statement for reporting a clinical trial protocol [15]. The SPIRIT checklist is provided in Additional file 1.

## Discussion

We have designed a randomised controlled study to compare two IVI regimens to treat CRC postoperative anaemia in terms of change in Hb levels from POD 1 to POD 30. Other variables, such as percentage of patients presenting with normal Hb levels at POD 30, changes in iron metabolism parameters, safety of both IVI regimens and complications and QoL, have been considered.

According to our procedures, patients with preoperative anaemia follow an optimisation treatment with the aim of reaching adequate levels before surgery and thus minimising postoperative anaemia and the need for transfusions. In addition, in our hospital, all patients receive 200 mg of iron sucrose right after surgery to account for surgical blood loses. There are no clear recommendations on the use and efficacy of postoperative iron treatment, especially in patients who have already received IVI before surgery. In these cases, the risk of iron overload has not been demonstrated. However, there are a large number of patients who arrive at the postoperative period with Hb levels lower than desired [16, 17]. This may lead to complications, a longer hospital stay and eventually to a slower recovery.

Currently, CRC patients without surgical complications are discharged after 3–4 days. This implies that, for some patients, the treatment with fractionated IVI cannot be completed to the calculated doses and thus they are prescribed oral iron after discharge. However, the absorption of oral iron in this context is known to be minimal [1, 8–10, 12] and, together with the low compliance expected due to mild but unpleasant side effects, patients end up receiving doses lower than required. To overcome these problems, a single dose of 1000 mg is an option for patients with lower Hb levels. However, the high cost of this formulation from a commercially available brand results in an underuse of this regimen in this setting as evidenced in a previous study [14]. Thus, it is of importance to assess whether, in patients with Hb levels < 11 g/dL, treatment with single doses of IVI may lead to larger increases in Hb levels and if this benefit depends on POD 1 Hb levels or other characteristics of patients, in order to make evidence-based decisions.

One of the main limitations of the study is the lack of blinding. Masking of the different administration schedules would need a double dummy strategy which would modify the pragmatic approach of the study. Additionally, the manufacturing of placebo and the masking procedures are a hurdle for an investigator-initiated study, needing the logistic and economic support, in most cases, of the marketing authorisation holder, a situation which is not desirable for an independent trial. On the other hand, the main endpoint is based on an analytical parameter and thus it is less prone to be affected by observation bias.

In addition, while we consider that studying the QoL is a relevant endpoint, we foresee that changes in QoL will be difficult to interpret due to the health condition of patients before surgery.

In a previous observational study [14], we observed that patients treated with postoperative IVI, increased Hb levels in about 2 points at POD 30. Despite these increases, a considerable number of patients do not reach normal levels. Thus, we expect changes of this magnitude and expect them to be larger with the single dose of ferric carboxymaltose than with the fractionated doses regimen with iron sucrose. We also hypothesise that patients with lower Hb levels will benefit more from the single-dose regimen.

The study is being performed in only one centre and, in most cases, the principal investigator, an anaesthetist, is responsible for the inclusion, randomisation and treatment of the patient, ensuring uniformity of procedures. Additionally, adapted risk monitoring has been implemented to ensure that the protocol is performed according to GCP criteria and to ensure the quality of data.

The results of this study will confirm whether the single dose of 1000 mg of ferric carboxymaltose should be preferred ahead of the fractionated doses and in which type of patients this regimen should preferably be used.

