**Discussion:**

The results of this study will confirm if the single dose of 1000 mg ferric carboxymaltose should be preferred in front of the fractionated doses and in which type of patients this regimen should be used preferably.

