### Statistical methods

#### Sample size

Our hypothesis is that the difference in change in Hb levels (primary endpoint) between the two studied regimens will be 0.75 g/dL. With a two-sided risk of 5% and a power of 80%, and assuming a common standard deviation of 1.3, a total of 48 evaluable patients per group are to be included.

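### The article says the results will confirm which patients should get the single dose, but the trial is sized for the overall effect only and has about 29% power for a between-stratum difference of 0.75 g/dL

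*Protocol article*

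**What the plan says.** Two places make a confirmatory claim about the type of patient. The last sentence of the main Discussion says the results will confirm whether the single dose should be preferred and "in which type of patients this regimen should preferably be used". The Discussion paragraph of the abstract says the same: "in which type of patients this regimen should be used preferably". The main Discussion also gives a direction: "We also hypothesise that patients with lower Hb levels will benefit more from the single-dose regimen". It states no size for that extra benefit.

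The means are in Inferential statistics. There is one line on strata, "A subgroup analysis for the stratification variable" (Hb below 10 against 10 g/dL or more, the cut used to stratify randomisation), and a multivariate analysis that the article itself calls exploratory.

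The Sample size section addresses the overall comparison only. The hypothesis is that "the difference in change in Hb levels (primary endpoint) between the two studied regimens will be 0.75 g/dL", and on that basis "a total of 48 evaluable patients per group are to be included".

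**The concern.** Saying that patients with lower Hb benefit more, or that one type of patient should get the single dose by preference, is a statement about a treatment-by-Hb interaction. Nothing in the article sizes the trial for one. The claim to confirm therefore conflicts with a sample size built on the main effect and with the exploratory label on the patient-type search.

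The conclusion would be used. The Background and Discussion explain that cost and limited perceived evidence hold back the 1000 mg product, and that the trial should show whether its benefit depends on POD 1 Hb so that decisions can rest on evidence. A chance contrast between strata could be reported as the confirmed answer on who should receive it. Equally, a non-significant interaction from an underpowered comparison could be taken to show that Hb level does not matter.

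**Working it through.** **Inputs.** From Sample size: difference 0.75 g/dL; "assuming a common standard deviation of 1.3"; "With a two-sided risk of 5% and a power of 80"%; 48 per group. From Randomisation: two strata, split at POD 1 Hb of 10 g/dL. Assumed, because the article does not give them: the stratum split (50:50, with 20:80 as the extreme) and the gain in precision from ANCOVA (none, with a correlation of 0.5 as the favourable case).

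**1. The plan's own figure.** n per group = 2 × (1.960 + 0.842)² × 1.3² / 0.75² = 47.2, rounded up to 48. Power at 48 is 80.7% by the normal approximation and 79.9% by the noncentral t. The stated size is reproduced for the overall difference.

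**2. Precision of the interaction.** With n_A and n_B patients per arm in the two strata, SE = SD × √(2/n_A + 2/n_B).

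- Equal strata (24 and 24 per arm): 1.3 × √(4/24) = 0.531 g/dL. This is twice the SE of the overall effect, 1.3 × √(2/48) = 0.265.
- 20:80 split (9.6 and 38.4 per arm): 1.3 × √(0.2083 + 0.0521) = 0.663 g/dL.

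**3. Power for the interaction.** Power is Φ(δ/SE − 1.96) plus a negligible opposite tail. The difference detectable with 80% power is 2.80 × SE. The total needed for 80% power at 0.75 g/dL is 96 × (detectable difference / 0.75)².

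| Case | Power at 0.75 g/dL | Detectable at 80% | Total N for 0.75 g/dL |
|---|---|---|---|
| SD 1.3, 50:50 | 29% | 1.49 | about 377 |
| SD 1.3, 20:80 | 20% | 1.86 | about 590 |
| SD 1.126 (ANCOVA, correlation 0.5), 50:50 | 37% | 1.29 | about 283 |

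The reduced SD is 1.3 × √(1 − 0.5²) = 1.126. For scale, at SD 1.3 with equal strata, power reaches only one half at 1.96 × 0.531 = 1.04 g/dL.

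**4. What if the strata were read by separate significance?** The article does not say they will be, so this is conditional. Suppose the true effect is the same in both strata, so that there is no interaction. With power p in each of two equal strata, the chance that exactly one is significant is 2p(1 − p). Using the t test, 24 per arm and SD 1.3:

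| Common true effect (g/dL) | Power per stratum | Exactly one significant |
|---|---|---|
| 0 | 5.0% | 9.5% |
| 0.5 | 25.7% | 38% |
| 0.75 | 49.9% | 50% |
| 1.0 | 74.2% | 38% |
| 1.25 | 90.3% | 17.5% |

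At 0.75 g/dL the figure is 54% for a 1:2 split and 61% for 20:80. An interaction test would hold the same error at 5%.

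**The case against.** The strongest reply is that the article describes no faulty method. It says a subgroup analysis by stratum is planned; it mentions no within-stratum tests and no rule for recommending treatment from them. An interaction test fits that sentence equally well, and such detail is commonly left to an analysis plan, which is not shown. The cut at 10 g/dL is prespecified and is the randomisation stratum. Elsewhere the article is careful: the multivariate search is called exploratory, the low-Hb idea is called a hypothesis, and the Discussion speaks of assessing whether the benefit depends on POD 1 Hb. The conflict lies in one closing sentence and its counterpart in the abstract, and the primary comparison is untouched.

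Most of this stands, and it rules out three stronger readings that a reader might infer.

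- *The trial would suggest a false difference about half the time.* This needs separate-significance reading, which the article does not announce, and a common effect near 0.75 g/dL. With equal strata 50% is the maximum of 2p(1 − p). It also counts both directions; only half of it, about 25%, would falsely favour the low-Hb stratum as hypothesised.
- *The trial cannot show effect modification.* Too absolute: a difference of about 1.5 g/dL would be found with about 80% power.
- *The absence of a named interaction test is itself an error.* It may be in the unseen plan.

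What the reply does not remove is the claim to confirm. Even with an interaction test specified, power for 0.75 g/dL is 20% to 29% at SD 1.3, and about 37% in the favourable ANCOVA case.

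**Conclusion.** The point holds as a mismatch between a stated conclusion and the design behind it. The article promises to confirm the type of patient, but its sample size supports only the overall difference. With 96 evaluable patients, SD 1.3 and equal strata, power for an interaction of 0.75 g/dL is about 29%, and 80% power needs about 1.5 g/dL, twice the planned main effect. A 20:80 split worsens these to about 20% and 1.9 g/dL. Confirmation is therefore unlikely unless the effect differs between strata by considerably more than the trial expects overall.

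This rests on the article's SD and sample size and on an assumed stratum split. The 50% figure for separate-significance reading is a warning about one possible misreading, not a property of the plan as written. The primary endpoint, its test and its sample size are not in question here. The change is worth making because it alters what the trial may conclude on one of its declared aims.

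**What to change.** 1. Base any subgroup conclusion on a treatment-by-POD 1 Hb interaction added to the planned ANCOVA, using the randomisation stratum and optionally also continuous Hb as a second look. Leave the primary model for the overall effect as it is.
2. Report the interaction estimate with its confidence interval, beside the treatment effect in each stratum with its confidence interval.
3. In the abstract's Discussion paragraph and the last sentence of the main Discussion, say that the trial will explore, not confirm, the type of patient in whom the single dose is preferable.

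Using continuous Hb only, dropping stratum p-values or changing the analysis population is not needed to answer this point; those are preferences or separate questions. The cost is one model term and a wording change, with no extra patients, visits or data. The interaction term does not raise the power, so the wording change is needed as well. The downside is a more modest claim.
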